### Sub-study 1: the quantitative study

#### Aim

The aim of the quantitative part is to measure the effects of the PC+ intervention on the population’s health, patients’ experience of care and health-care costs. To measure the effects the researchers will use the following sources: patient questionnaires, data from the cardiology PC+ centre, data from the regional hospital and health insurance claims data. The data will be collected at four different time points, namely at baseline, before the patient has the first consultation with the cardiologist (T0), a week after the first consultation (T1), 3 months after the first consultation (T2) and 6 months after the first consultation (T3). The outcome parameters, including the dimensions, outcomes, concepts, methods and time frame, are summarized in Table 1.

**Table 1 Tab1:** Overview of the outcome measurements

Dimension	Outcome measure	Concept	Method	Data collection time			
				T0	T1	T2	T3
Population’s health	Health status, health-related quality of life	EQ-5D-5 L	Questionnaires	X	X	X	
		EQ-VAS		X	X	X	
		SF-12		X		X	
Experience of care	Effectiveness	EQ-5D-5 L	Questionnaires	X	X	X	
		Number of referrals	Data^a^	X		X	X
	Timeliness	Time between referral of the GP and appointment at the PC+ centre/hospital	Questionnaires	X	X		
	Patient centred	Questions about the experiences of patients with health care	Questionnaires		X		
	Safety	% Hospital admissions	Data^a^				X
		% Emergency care visits					X
	Equity	Subgroup analysis, e.g. educational level and age	Questionnaires	X		X	
Health-care costs	Health-care costs: primary care, PC+, secondary care and diagnostics	Health insurance claims data	Data^a^				X
	Efficiency	Number of consultations	Data^a^				X
		% Hospital admissions					X
		% Patients referred to hospital after PC+					X

T0 – at baseline: before the consultation

T1 – within a week after the consultation

T2 – 3 months after the consultation (follow-up)

T3 – 6 months after the consultation (follow-up)

^a^Data of the PC+ centre, the hospital and Vektis

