### Data collection

#### Patient questionnaire

All participating patients will be asked to complete questionnaires at three different time points, namely at baseline (e.g. before the consultation with the cardiologist (T0)), within a week after the consultation (T1) and at three-month follow-up after the consultation (T2). The baseline questionnaire (T0) consists of questions about the demographics and health of the patient. Questionnaire 2 (T1) consists of questions about the health of the patient and about the patient’s experience of care. Questionnaire 3 (T2) consists only of questions about the health of the patient. All patients who signed the informed consent, but of whom the researchers did not receive the questionnaire yet, will be kindly reminded to complete the questionnaire. Patients will receive up to two reminders, one by phone and one by a regular mail. Moreover, all outcome parameters are explained in one of the following sections.

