#### Experience of care

The experience of care will be measured using the perspective of the patient, i.e. the patient’s interaction and experience with the health-care system. The outcome parameters are based upon the six dimensions of health-care performance of the IOM: safety, effectiveness, equity, timeliness, patient-centredness and efficiency [19]. As mentioned above, efficiency will be included in the dimension health-care costs.

Effectiveness of care will be measured with the EQ-5D-5 L questionnaire and the percentage of referrals to hospital-based outpatient cardiology care. On the one hand, effectiveness will be measured using the EQ-5D-5 L scores, where it is analysed whether the health of the population is improved after a follow-up of 3 months. On the other hand, effectiveness will be measured using the number of referrals to hospital-based outpatient cardiology care, where it is analysed whether this number is decreased in the period from 2013 to 2017.

Timeliness of care will be examined by measuring the waiting time (in days) between the day the patient is referred by his GP and the day of the first consultation with the cardiologist.

Patient-centred care will be measured using items based on the Consumer Quality (CQ) index. The CQ index is a standardized method for measuring experiences of patients with health care [38]. The questionnaire (T1) includes 30 questions about the experiences of the patients with health care, with specific regard to their experiences with the health-care professionals (e.g. *‘Did you feel welcome and at ease?’* and *‘Did the health-care professionals listen attentively?’*).

Safety of care will be measured using data that will be made available by the hospital concerning: 1) hospital admissions; 2) emergency care visits.

Equity of care will be examined by performing subgroup analysis on all outcome measures regarding educational level (high versus low) and age (lower than median and higher than median).

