### Sample size and power calculation

The sample size and power calculation is based on the referral data of the hospital in 2013 extracted from its registration system. The data of 2013 show that 12% (1755 referrals to hospital-based outpatient cardiology care) of all referrals (14,978 referrals) to the cardiology department of the hospital are eligible for PC+. These eligible patients are referred to hospital-based outpatient cardiology care, which provides, among other health care, the same health care as the PC+ centre. A decrease of 50% in the number of referrals to hospital-based outpatient cardiology care is seen as a relevant difference. So, the number of referrals eligible for PC+ will decrease from 1755 (12% of the total referrals to cardiology) referrals to 878 (6% of the total referrals to cardiology). While assuming a power of 80% and a significance level of 0.05, 358 patients per group (intervention as well as control) are required. Taking into account a dropout of 20%, a sample size of 429 patients per group is required, so this study needs to include 858 patients in total.

To calculate the sample size the following formula was used to compare proportions:$$ N=\frac{{\left({Z}_{\alpha }/2+{Z}_{\beta}\right)}^2\ast p\kern0.2em \left(1-p\right)\left(r+1\right)}{{\left({p}_{0-}\kern0.2em {p}_1\right)}^2\ast r} $$

With the following meaning of the abbreviations:

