#### Data analysis

To investigate the effect of PC+ on population health, patients’ experience of care and health-care costs an intention to treat analysis will be conducted. The between-group comparisons will be analysed with multilevel analysis to account for the dependency of observations in time. We will apply a two-level linear mixed model (time, participants) and the level of statistical significance will be set at 0.05 (two-tailed). Separate models (random intercept) will be set up for each outcome measure. The independent variables in each model are a dummy variable indicating the group (control group = reference category), three dummy variables for time (T0 = reference category) and the interaction variable between group and time.

To correct for the possible confounding influence of baseline characteristics of the patients (e.g. age, gender, level of education, native country and health-care costs) and the GP characteristics (e.g. age, gender and practice) a propensity score will be added into the multilevel model. The propensity score will be estimated using a logistic regression model with treatment group (control or intervention) as dependent variables and baseline variables (patient and GP characteristics) included as independent variables. Only baseline variables that are related to the outcome variable (with a *p*-value smaller than 0.10) are included in the propensity score [25].

If normality assumptions are violated, outcome variables will be log-transformed and if necessary non-parametric tests will be used.

SPSS version 22 is used to analyse the data.

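### For EQ-5D-5L and EQ-VAS, a random intercept alone gives one pooled standard error to two differently spaced changes; if correlation falls with time, the three-month interval is somewhat too narrow

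*Protocol article*

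**What the plan says.** All statements are in the protocol article.

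- **Model.** Under Data analysis: "We will apply a two-level linear mixed model (time, participants) and the level of statistical significance will be set at 0.05 (two-tailed"), followed by "Separate models (random intercept) will be set up for each outcome measure". The fixed effects are group, "three dummy variables for time (T0 = reference category) and the interaction variable between group and time". No random slope, residual structure or robust standard error is named.
- **Visits.** The Aim section of sub-study 1 places questionnaires at baseline, "a week after the first consultation (T1), 3 months after the first consultation (T2"). The Patient questionnaire section repeats this as "within a week after the consultation (T1) and at three-month follow-up after the consultation (T2"). T1 and T2 are both timed from the consultation. T0 comes before it, with no stated lead time.
- **Outcomes.** Table 1, "Overview of the outcome measurements", marks EQ-5D-5L and EQ-VAS at T0, T1 and T2, and SF-12 at T0 and T2 only. Patient-centredness appears once (T1), and so do costs, admissions and emergency visits (T3). The number of referrals is marked at T0, T2 and T3, but the Experience of care section describes it as a count over calendar years, so it is not part of this point.
- **Use of the three-month score.** The Experience of care section states "effectiveness will be measured using the EQ-5D-5 L scores, where it is analysed whether the health of the population is improved after a follow-up of" (the period it names is three months). No outcome is named primary.

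**The concern.** A random intercept with independent residuals implies the same variance at every visit and the same correlation between every pair of visits. The model then estimates one variance of change and applies it to both the T0-to-T1 and the T0-to-T2 group-by-time terms. T1 falls within a week after the consultation and T2 three months after it, so equal correlation is a special case that the design gives little reason to expect.

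If the T0–T2 correlation is lower than the average over the three pairs, the pooled figure understates the uncertainty of the three-month contrast. Its confidence interval is then too narrow and its test rejects too often. The three-month EQ-5D-5L comparison is one of the article's stated effectiveness measures and is tested at two-sided 0.05, so this bears on a claim the study intends to make.

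**Working it through.** **Inputs.** From the documents: random intercept only (Data analysis), three visits for EQ-5D-5L and EQ-VAS (Table 1), two-sided 0.05. The documents give no variance, correlation or standard error for these outcomes, so every correlation below is an assumption.

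**The plan's own figure.** The only related number is the sample size: "While assuming a power of 80% and a significance level of 0.05, 358 patients per group (intervention as well as control) are required". The article's formula gives (1.96 + 0.84)² × 0.09 × 0.91 × 2 / 0.06² = 356.7, so 357, which agrees closely with 358. It rests on referral proportions and serves here only to set the scale of a simulation.

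**Formulas (complete data, three visits).** The random-intercept model's variance of any change is 2 × (mean variance − mean covariance). The true variance of a change from visit a to visit b is Va + Vb − 2Cab. With all variances set to 1 and ρ̄ the mean of the three correlations:

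- ratio of model to true standard error for T0-to-Tk = √[(1 − ρ̄)/(1 − ρ0k)]
- actual error rate = 2 × [1 − Φ(1.96 × ratio)]

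So, with equal variances, the T0-to-T2 standard error is too small exactly when ρ02 is below the average of the three correlations. The T0-to-T1 standard error is too large exactly when ρ01 is above it.

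**Worked case, 0.80/0.60/0.65 (T0T1/T0T2/T1T2).** ρ̄ = 2.05/3 = 0.683. T0-to-T2: √(0.317/0.40) = 0.89, error rate 8.1%. T0-to-T1: √(0.317/0.20) = 1.26, error rate 1.4%.

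**Range, equal variances.**

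| Assumed ρ01/ρ02/ρ12 | T0–T2 ratio | Actual error | T0–T1 ratio | Actual error |
|---|---|---|---|---|
| 0.70/0.70/0.70 (flat) | 1.00 | 5.0% | 1.00 | 5.0% |
| 0.61/0.54/0.61 (T0 well before T1) | 0.95 | 6.3% | 1.03 | 4.4% |
| 0.75/0.65/0.70 | 0.93 | 7.0% | 1.10 | 3.2% |
| 0.80/0.60/0.65 | 0.89 | 8.1% | 1.26 | 1.4% |
| 0.80/0.50/0.55 | 0.88 | 8.6% | 1.38 | 0.7% |
| 0.85/0.50/0.55 | 0.86 | 9.3% | 1.56 | 0.2% |
| 0.65/0.60/0.70 | 0.94 | 6.7% | 1.00 | 5.0% |
| 0.60/0.60/0.75 (status shifts at the consultation) | 0.94 | 6.7% | 0.94 | 6.7% |

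**Unequal variances.** Take flat correlation 0.70 with the T2 standard deviation 15% lower. Mean variance = (1 + 1 + 0.7225)/3 = 0.9075; mean covariance = (0.70 + 0.595 + 0.595)/3 = 0.63; model variance = 2 × 0.2775 = 0.555. The true variances are 0.5325 (T0-to-T2) and 0.60 (T0-to-T1), giving ratios of 1.02 and 0.96: both directions reverse, slightly. With 0.80/0.60/0.65 and the same lower standard deviation, the ratios are 0.90 and 1.20.

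**Two visits (SF-12).** With a single pair of visits, mean variance and mean covariance belong to that pair, so model and true variance of change coincide. The ratio is 1.00 whether or not the two standard deviations are equal.

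**Simulation.** In 120 REML fits with 358 per group and 0.80/0.60/0.65, the model standard error was 0.0594 for both interactions. The theoretical values are √(2 × 0.4/358) = 0.0473 for T1 and √(2 × 0.8/358) = 0.0669 for T2. The empirical standard deviations were 0.0443 and 0.0623, each about one Monte Carlo error (roughly 6.5%) below theory. The run confirms the single pooled standard error; the size of the T2 understatement rests on the formula, since 120 fits are too few to fix it.

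**The case against.** The strongest reply is that the consequence is conditional. The documents give no correlations or variances, and with flat correlations and equal variances there is no error at all. That stands.

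A reader might infer that the T0-to-T2 standard error is certainly too small and the T0-to-T1 one certainly too large, on the view that T0 and T1 are a week apart. The documents do not support this. The week runs from the consultation to T1, the lead time of T0 is not stated, and the consultation itself lies between T0 and T1 while T1 and T2 both follow it. T0–T1 need not be the most correlated pair, and the table shows its error vanishing or reversing.

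A reader might also treat the three-month change as the trial's key contrast. The article lists it as one of two effectiveness measures, names nothing primary, and bases the sample size on referral proportions, which this issue does not touch.

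Finally, the article does not say that residuals are independent, and an analysis plan that is not shown could add a residual structure. That is fair as to where the repair can be made. But the article does choose a model and names only the random intercept, so this is a stated method that can be improved, not a missing detail.

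**Conclusion.** The point holds in a limited form. As written, the model gives EQ-5D-5L and EQ-VAS one pooled standard error for two changes over different intervals. If correlation falls with time and variances are roughly equal, the T0-to-T2 standard error is about 5–14% too small and the actual error rate about 6–9% at a nominal 5%. Among the patterns examined, the T0-to-T2 ratio exceeded 1 only with flat correlation and a lower T2 standard deviation, and then by 2%. No direction can be claimed for T0-to-T1: its ratio ran from 0.94 to 1.56.

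The effect is on standard errors. With complete data the group-by-time estimates are the same differences in mean change under either covariance. SF-12 with complete data and the single-time outcomes are not affected. The size is modest, but the remedy is nearly free, so the change is worth making before analysis.

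**What to change.** For EQ-5D-5L and EQ-VAS, replace the random intercept with an unstructured within-patient covariance over T0, T1 and T2. State the fallback in advance in case it does not converge: either a simpler heterogeneous structure or robust standard errors. If heterogeneous Toeplitz is the structure chosen, note that it still sets the T0–T1 and T1–T2 correlations equal. The random intercept can stay for SF-12.

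The cost is four variance parameters: six (three variances, three covariances) in place of two. That is negligible with the 358 to 429 patients per group foreseen under Sample size and power calculation. Nothing is lost in validity if the correlations turn out flat.

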#### Population health

Population health will be measured with three generic validated questionnaires, namely the EQ-5D-5 L, the EQ-VAS and the Short Form Health Survey (SF-12).

The EQ-5D-5 L incorporates descriptions and valuations of health status and reflects how patients value their own health state. The questionnaire comprises the dimensions mobility, self-care, usual activities, pain/discomfort and anxiety/depression [28, 29]. The scores range from −0.33 to 1 (worst imaginable to best imaginable health state), using the Dutch utility tariff [30]. Instead of the EQ-5D-3 L 3-level version, we have chosen to use the EQ-5D-5 L 5-level, because this appears to be a valid extension of the 3-level. Several studies indicate that the measurement properties of the EQ-5D-5 L are superior to the EQ-5D-3 L in terms of feasibility, reliability, ceiling effects, discriminatory power and convergent validity [31–33].

The EQ-VAS (visual analogue scale) is added; this is a reflection of how patients value their own health state (range from 0 to 100).

The SF-12 is a subset of the larger SF-36 [34]. The questionnaire comprises eight health aspects, namely physical functioning, role limitations because of physical health problems, bodily pain, general health, vitality (energy/fatigue), social functioning, role limitations because of emotional problems, and mental health (psychological distress and psychological well-being) [34–37]. The reliability of the SF-12 is high (> 0.80) [34–37]. In addition, three items from the SF-36 are added to calculate the Mental Health Inventory score, comprising the dimensions feeling nervous, feeling downhearted and blue, and feeling happy [34].

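### The single repeated-measures model set for every outcome does not match the Table 1 schedule and cannot be run for outcomes measured once, and its log or rank fallback suits neither costs nor EQ-5D

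*Protocol article*

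**What the plan says.** The Data analysis section covers population health, experience of care and health-care costs together. It states "We will apply a two-level linear mixed model (time, participants", so the levels are measurement occasions within patients, and "Separate models (random intercept) will be set up for each outcome measure". The predictors in each model are a group dummy, "three dummy variables for time (T0 = reference category) and the interaction variable between group and time". A propensity score built from patient and GP characteristics is added. The only alternative offered is: "If normality assumptions are violated, outcome variables will be log-transformed and if necessary non-parametric tests will be used".

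The Aim of sub-study 1 says "The data will be collected at four different time points", but that describes the study as a whole. For the questionnaires, "All participating patients will be asked to complete questionnaires at three different time points" (T0, T1, T2). Patient-centredness is asked once: "The questionnaire (T1) includes 30 questions about the experiences of the patients with health care". Table 1 places costs, admissions, emergency visits, consultations and referral after PC+ at T3 only. For the EQ-5D-5L utility, "The scores range from −0.33 to 1".

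**The concern.** Three time dummies with T0 as reference need data at T0, T1, T2 and T3. If no outcome is collected at all four, the rule cannot be followed as written for any outcome. Where an outcome is collected once, there is no baseline and no change over time to compare between groups.

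The single-time outcomes include all cost outcomes, both safety outcomes and patient-centredness. If the stated rule cannot be applied to them, the analyst must choose another model, possibly after seeing the data, in a non-randomised comparison that relies on adjustment. The stated fallback does not close the gap. It changes the cost question, it cannot be applied to part of the EQ-5D range, and the usual rank tests have no place for a propensity term.

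**Working it through.** **1. Schedule against model.** The stated fixed part has 8 columns: intercept, group, three time dummies and three group-by-time terms. An outcome measured at k times in two groups gives 2k group-by-time cells, so the rank is at most 2k and k − 1 time dummies can be estimated.

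| Outcome (Table 1) | Times | k | Rank (8 needed) | Time dummies supported |
|---|---|---|---|---|
| EQ-5D-5L, EQ-VAS | T0, T1, T2 | 3 | 6 | 2 |
| SF-12 | T0, T2 | 2 | 4 | 1 |
| Referrals | T0, T2, T3 | 3 | 6 | 2 |
| Timeliness | T0, T1 | 2 | 4 | 1 |
| Patient-centredness | T1 | 1 | 2 | 0 |
| Costs, admissions, emergency visits, consultations | T3 | 1 | 2 | 0 |

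No row reaches 8. Timeliness is marked at two times, but the Experience of care section defines it as the days from referral to first consultation, which is one value per patient. With one value per patient, only the intercept and group effect remain, and the random-intercept variance cannot be separated from the residual variance.

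**2. Outcome type.** Table 1 gives admissions and emergency visits as percentages. Data of the regional hospital collects them as numbers, and the Health-care costs section defines an average number of admissions and of consultations per patient. They are therefore binary or counts, depending on the passage. The only model named is linear, and neither a log nor a rank test mends a binary outcome.

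**3. Log fallback for costs.** The plan's formula gives (1.96 + 0.84)² × 0.09 × 0.91 × 2 / 0.06² = 356.7 per group, close to the stated 358; the inflated figure is 429. After the planned 20% dropout, 429 × 0.8 = 343 per group.

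Assume lognormal costs with equal arithmetic means and log-SDs s₀ and s₁. A lognormal mean is exp(μ + s²/2), so equal means imply a log-scale difference of (s₁² − s₀²)/2. Its standard error is √[(s₀² + s₁²)/343], and z is their ratio. The chance of a two-sided 5% rejection is P(Z > 1.96 − z) + P(Z < −1.96 − z).

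| Assumed log-SDs | Log difference | SE | z | Rejects | Geometric mean appears lower by |
|---|---|---|---|---|---|
| 1.0 v 1.0 | 0 | 0.076 | 0 | 5% | 0% |
| 1.0 v 1.05 | 0.051 | 0.078 | 0.65 | 10% | 5% |
| 1.0 v 1.1 | 0.105 | 0.080 | 1.31 | 26% | 10% |
| 1.0 v 1.2 | 0.220 | 0.084 | 2.61 | 74% | 20% |
| 1.0 v 1.3 | 0.345 | 0.089 | 3.90 | 97% | 29% |

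Simulation with 4,000 runs agrees for the last two rows (74% and 97%); a test of arithmetic means on the same data rejected 5% and 6%. The group with the wider spread looks cheaper, whichever group that is.

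**4. Log fallback for EQ-5D.** The stated range starts at −0.33, and the log does not exist at or below zero.

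**5. GP level (secondary).** There are 858 patients and about 135 GPs, so 858/135 = 6.36 per GP. The design effect is 1 + (6.36 − 1) × ICC. The document gives no ICC; an assumed 0.01 gives 1.05 and 0.05 gives 1.27. These are upper guides, because one GP can refer to both settings.

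**The case against.** The strongest reply is that this is a condensed article. The mixed model is introduced to handle dependency over time, the missing-data section separately recognises non-repeated measures, and outcome-specific models normally belong in an analysis plan. That would answer a complaint of missing detail. It does not answer this point, because the article states a rule for each outcome that contradicts its own schedule, and it recognises non-repeated measures only for imputation.

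Several limits do stand:

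- A reader might infer that the model is useless for every outcome. It is not: EQ-5D-5L, EQ-VAS and SF-12 have a baseline and follow-up, and only the dummy count is wrong.
- A reader might infer that whole aims cannot be analysed. The experience aim also uses repeated EQ-5D-5L scores and a 2013–2017 referral trend that is not a two-group patient model. Referral after PC+ exists in one group only and needs no between-group model.
- Zero total cost is implausible. Under Health insurance claims data the window opens at referral and covers GP, PC+ and hospital care, so zeros would arise mainly in cost components.
- The log-SDs are assumptions. With equal spread the log test holds its 5% level, and the matter arises only if the fallback is used.
- The article names no rank test and does not say that the propensity adjustment is given up. Its loss is likely with standard tests, but not stated.
- GP age, gender and practice enter the propensity score, so GP confounding is addressed. Only the dependence between patients of one GP is left out.

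**Conclusion.** The point holds as a contradiction between the stated model and the stated schedule. It is minor for the repeated health outcomes. It is substantive for patient-centredness, costs, admissions, emergency visits and consultations, where the model as written cannot be fitted; timeliness belongs with them in substance.

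The cost fallback answers a different question from the article's premise of reduced health-care costs. How far it misleads depends on how much the spread differs between groups: false rejection runs from 5% with equal log-SDs to 26% at 1.0 v 1.1 and 74% at 1.0 v 1.2, all assumed values with equal true means and 343 per group. Unequal spread is plausible, since the Study population section directs less severe patients to PC+, but the documents give no cost variances. It would therefore go too far to conclude that the cost result will be wrong.

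GP clustering is a refinement, with a design effect of at most about 1.05 to 1.27 at an assumed ICC of 0.01 to 0.05. The documents do not support treating it as a flaw that invalidates the standard errors.

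**What to change.** - Limit the mixed model to repeated outcomes, with dummies that match their schedule: two for EQ-5D-5L and EQ-VAS, one for SF-12.
- For single-time outcomes, including waiting time, use one row per patient with group and propensity score, and a link suited to the outcome. First reconcile the percentages in Table 1 with the numbers in Data of the regional hospital and Health-care costs. Then use logistic regression where the outcome is any event, and a count model (for example negative binomial) where it is a number.
- Compare arithmetic mean costs, by a gamma model with log link or by bootstrap, keeping the propensity score.
- Replace the log and non-parametric fallback by robust or bootstrap standard errors in the same adjusted model.
- Optionally, account for the referring GP by a random intercept or cluster-robust errors. The PC+ centre records the GP's name, and the hospital data are described as similar.

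The cost is revised analysis text, modest extra programming and possibly slightly wider standard errors. Data collection and sample size need not change.
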